## Expected Adverse Events and Serious Adverse Events

Due to the population of the study sample, the following events could be expected to occur throughout the duration of the trial and will therefore not be collected or reported to the sponsor:

- Outpatient appointments, including GP appointments, or treatments for ongoing conditions that were present at the start of the study

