# Recording and reporting of serious adverse events (SAEs)

## Definitions

Table 4.Definitions for SAEs

| **Term** | **Definition** |
| --- | --- |
| Adverse Event (AE) | Any untoward medical occurrence in a participant or clinical investigation, which does not necessarily have to have a causal relationship with this treatment.  An AE can therefore be any unfavourable and unintended sign (including an abnormal laboratory finding), symptom or disease temporally associated with the study, whether or not considered related to the study. |
| Serious Adverse Event (SAE) | A serious adverse event is any untoward medical occurrence that:   - Results in death - Is life-threatening* - Requires inpatient hospitalisation or prolongation of existing hospitalisation - Results in persistent or significant disability/incapacity - Consists of a congenital anomaly or birth defect - Other important medical events**   *The term "life-threatening" in the definition of "serious" refers to an event in which the participant was at risk of death at the time of the event; it does not refer to an event which hypothetically might have caused death if it were more severe.  **Other ‘important medical events’ may also be considered serious if they jeopardise the participant or require an intervention to prevent one of the above consequences. |

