## Reporting Procedures for Serious Adverse Events

All SAEs (except from those outlined as expected) occurring from the time of randomisation until the final study visit must be reported to the Sponsor immediately and within 24-hours of becoming aware of the event. The SAE will be reported using appropriate forms and according to the Sponsor SOP for reporting serious adverse events. Additional information will be provided if requested to the Sponsor and main Research Ethics Committee (REC). The PI or a delegated physician (as agreed by the Sponsor) is responsible for the review and sign off of the SAE and the assessment of causality (i.e., whether an event is related to a study procedure or intervention).

The Sponsor will perform an initial check of the information and ensure that the SAE line listing is reviewed by the Director of Research & Innovation. All SAE information must be recorded on an SAE form and sent to the Sponsor. Additional information received for a case (follow-up or corrections to the original case) needs to be detailed on a new SAE form and sent to the Sponsor. Copies of all documentation and correspondence relating to SAEs will be stored in the trial master file (TMF).

For each **SAE** the following information will be collected:

- Full details in medical terms and case description
- Event duration (start and end dates, if applicable)
- Action taken
- Outcome
- Seriousness criteria
- Relationship to the study procedure or intervention

Any change of condition or other follow-up information should be emailed to the Sponsor immediately and within 24-hours of the information becoming available. Events will be followed up until the event has resolved or a final outcome has been reached.

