## Secondary trial outcome analysis

Outcomes at 12- and 24-weeks follow-up will be summarised by randomised group and overall using mean (SD) and median (IQR) for continuous variables and count (percentage) for categorical variables. The number of SAEs will be presented overall and by randomised group.  All exploratory analyses will be considered hypothesis generating rather than providing firm conclusions and no p values will be reported.

Outcome acceptability will be determined by quantifying the amount of missing data across the secondary outcomes. The proportion of missing data (number, %) will be reported for each outcome, but no imputation will be performed to account for this missing data. Reasons for missing data will be gathered where possible.

Quantitative acceptability data including:

- rates of uptake and engagement with each component of the PERSONAL-AGILITY intervention
- adherence to the intervention (e.g., frequency, intensity, time and type of activity)

will be reported descriptively using number and percentage.

PROMS relating to intervention acceptability (the 9-item shared decision-making questionnaire) will be examined descriptively, by reporting at 12- and 24-weeks follow-up using mean (SD) and median (IQR).

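### The expected-event exemption in section 8.3 has no stated limit, so it can be read to leave admissions for worsening of a baseline condition out of the SAE count

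*Protocol*

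**What the plan says.** Four places in the protocol bear on this.

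- **Section 8.1, Table 4.** An untoward medical occurrence is serious if, among other criteria, it "Requires inpatient hospitalisation or prolongation of existing hospitalisation".
- **Section 8.3.** The heading is "Expected Adverse Events and Serious Adverse Events". The list has a single item: outpatient and GP appointments, "or treatments for ongoing conditions that were present at the start of the study". Because such events are to be expected in this population, they "will therefore not be collected or reported to the sponsor".
- **Section 8.4.** The reporting duty carries a matching exception: "All SAEs (except from those outlined as expected) occurring from the time of randomisation until the final study visit must be reported" to the sponsor within 24 hours. The principal investigator or a delegated physician reviews each SAE and assesses causality.
- **Section 9.5.** "The number of SAEs will be presented overall and by randomised group". Chapter 9 plans no other tabulation of adverse events.

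**The concern.** The exemption waives collection as well as expedited reporting. Waiving an expedited report is common and does little harm, because the event stays in the database and can be counted later. An event that is never collected is absent from the trial's safety data, and no statistical analysis plan can restore it.

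The exempted category is also tied to the condition that defines the study group. Under section 5.1, everyone recruited as living with multiple long-term conditions and frailty has at least two such conditions, and the background section says that these people are admitted to hospital more often. Worsening of an existing condition after an increase in activity is a plausible harm of this intervention. It is also the kind of event that could be filed as treatment of an ongoing condition.

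Site staff have to decide what falls inside the exemption. By sections 6.6.1 and 6.7, neither the study team nor the outcome assessors are blinded, so an unclear boundary could be applied differently in the two arms.

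**Working it through.** The protocol states no admission or SAE rate, so there is no figure to reproduce. The check sets the sections side by side.

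**1. Is the exemption limited to non-serious events?** No. The heading of section 8.3 names serious events, and section 8.4 carries the exemption into SAE reporting. Nothing in 8.1 to 8.4 says that an event meeting a Table 4 criterion stays reportable when it concerns a pre-existing condition.

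**2. What can the treatments in section 8.3 mean?** Three readings fit the words.

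| Reading | What is exempt | Effect on the SAE count |
|---|---|---|
| A. Outpatient qualifies both appointments and treatments | Outpatient visits and outpatient treatment | Almost none: such care would not ordinarily meet a Table 4 criterion |
| B. Routine or planned treatment | Outpatient care and elective admissions for a baseline condition | Elective admissions not counted; acute worsening counted |
| C. Any treatment of a baseline condition | Also unplanned inpatient treatment | Admissions for worsening of a baseline condition not counted |

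**3. Does another section choose between them?** Not decisively. Under A the exception in section 8.4 has almost no content, which counts against A. Both B and C give it content, so section 8.4 does not establish C.

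**4. Would an exempted admission be captured elsewhere?** Not dependably.

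- The adverse event log in section 8.2 takes only events judged to be a direct result of study activities. An admission put down to the underlying disease would not enter it.
- The formal causality sign-off in section 8.4 is made on SAEs. An event classed as exempt at site need not reach it.
- Withdrawal records (section 7.8) would show an admission only if it led the participant to leave, and they do not feed the count in section 9.5.

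**5. Result.** Under C the number presented by arm in section 9.5 is an incomplete count of the events that Table 4 calls serious. Under A it is essentially complete. The protocol does not tell the reader, or the site, which of these applies.

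**The case against.** The strongest case against is that section 8.3 describes routine continuing care. It names no admission, exacerbation, deterioration or death. Table 4 speaks of an untoward occurrence that leads to hospitalisation. A treatment is not itself an untoward occurrence, but the deterioration behind it is, so an acute admission would still be reportable under section 8.4. Elective inpatient treatment is enough to give the section 8.4 exception a purpose. The sponsor's SOP, to which section 8.4 refers, may settle the matter. The SAE count is descriptive, and no progression criterion in section 9.4 uses it.

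Much of this stands. The narrower reading is reasonable and may well be the intended one. But the protocol does not state it, and the SOP is not available here. A count that is only described still needs a definite rule for what enters it.

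Some stronger readings are tempting but lack support:

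- **That the protocol excludes admissions, or most of them.** It does not say so, and no share can be derived.
- **That Table 4 is contradicted.** Table 4 classifies events, while 8.3 and 8.4 govern collection and reporting. The gap is that they are not tied together.
- **That falls would be lost.** Section 7.9.2 acknowledges a slightly raised falls risk for people who have fallen before. A fall during the trial is a new event, not treatment of an ongoing condition.
- **That every participant is affected.** The criterion of two or more conditions does not apply to carers.
- **That omitted events are beyond recovery.** Consent to medical-record access is sought at baseline (section 6.5), questionnaire responses of concern are reviewed (section 7.9.1), and interviews ask about unintended harms (section 7.7). These routes are partial, and none is planned as a source for the SAE count.

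**Conclusion.** The point holds as a defect of scope. Sections 8.3 and 8.4 waive both collection and SAE reporting for a category that has no stated limit, and one tenable reading places admissions for worsening of a baseline condition inside it. Those events would then be absent from the only planned tabulation of adverse events and could bypass causality review.

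The extent of any undercount cannot be derived from the documents. It depends on which reading sites adopt, on how often participants are admitted, and on how many admissions concern a baseline condition, and the protocol gives none of these. The conclusion assumes that sites follow the protocol text as written and that no sponsor procedure narrows it. It is worth correcting because data not collected during the trial are hard to replace and the correction is cheap.

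**What to change.** Reconcile sections 8.1, 8.3, 8.4 and 9.5.

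- In 8.3, limit the exemption to events that meet no Table 4 seriousness criterion.
- In 8.3 and 8.4, state that any event meeting such a criterion is collected and assessed for causality, even if it concerns a pre-existing condition.
- In 9.5, state that all such events are counted overall and by arm.
- If expected SAEs are to be treated more lightly, waive the 24-hour report only, not collection.

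The cost is a wording amendment and some additional SAE forms. Nothing changes in treatment, visits or sample size.

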## Reporting Procedures for Serious Adverse Events

All SAEs (except from those outlined as expected) occurring from the time of randomisation until the final study visit must be reported to the Sponsor immediately and within 24-hours of becoming aware of the event. The SAE will be reported using appropriate forms and according to the Sponsor SOP for reporting serious adverse events. Additional information will be provided if requested to the Sponsor and main Research Ethics Committee (REC). The PI or a delegated physician (as agreed by the Sponsor) is responsible for the review and sign off of the SAE and the assessment of causality (i.e., whether an event is related to a study procedure or intervention).

The Sponsor will perform an initial check of the information and ensure that the SAE line listing is reviewed by the Director of Research & Innovation. All SAE information must be recorded on an SAE form and sent to the Sponsor. Additional information received for a case (follow-up or corrections to the original case) needs to be detailed on a new SAE form and sent to the Sponsor. Copies of all documentation and correspondence relating to SAEs will be stored in the trial master file (TMF).

For each **SAE** the following information will be collected:

- Full details in medical terms and case description
- Event duration (start and end dates, if applicable)
- Action taken
- Outcome
- Seriousness criteria
- Relationship to the study procedure or intervention

Any change of condition or other follow-up information should be emailed to the Sponsor immediately and within 24-hours of the information becoming available. Events will be followed up until the event has resolved or a final outcome has been reached.

# Statistics and data analysis

In line with a convergent parallel mixed methods design, quantitative and qualitative data will be analysed separately before being integrated within a mixed methods analysis.^115^.

## Sample size calculation

Determinations of sample size from a power calculation around a primary outcome are not relevant to a feasibility study^116^ ^117^. Sample sizes of 24-50 are generally considered sufficient to assess the key uncertainties relating to feasibility^118,119^ ^120^ ^121^ ^122^. A sample size of *n*=50 people living with MLTCs and frailty is appropriate to the aims of this study.

## Summary of baseline data and flow of participants

A CONSORT diagram, based on the extension to randomised pilot and feasibility trials, showing the flow of participants through the study will be produced^123^. Data will be checked for outliers and missing values and validated using the defined score ranges. Baseline demographics will be summarised by treatment group and for the total population using number (percentage) for categorical variables and mean (standard deviation) for continuous variables (unless they are found to be skewed in which case median and interquartile range will be presented). Clinically meaningful differences between groups at baseline will be described, but no statistical testing will be conducted to compare baseline characteristics by treatment group^124^. The basic baseline characteristics (age, gender, frailty status and ethnicity) of those who participated and declined will be explored where possible.

## Primary trial outcome analysis

The number and percentage of people living with MLTCs and frailty and carers:

- Screened
- Eligible
- Ineligible
- Consented
- Retained at 12 and 24 weeks

Will be calculated separately and described using descriptive statistics and 95% confidence intervals. and presented within a CONSORT diagram ^124^,^125^

## Progression criteria

Judgement regarding the feasibility of a future definitive trial and the acceptability of the trial processes and intervention will be established using a set of *a priori*  ‘progression criteria’ for each of the  feasibility and acceptability outcomes ^126^, ^121^. Failure to achieve these pre-established criteria will not necessarily indicate that a full-scale trial is not viable. For each criterion, the development of ‘stop’ and ‘go’ thresholds have been pre-specified ^127^. The ‘stop’ thresholds indicate when there are issues that cannot be resolved, and ‘go’ thresholds when there are no issues that may impede the success of a trial. Results falling between these thresholds indicate that ‘change’ is required, and will allow the research team to identify where there are issues that may be remedied, rendering a definitive RCT viable^121^, ^127^. Overall decisions about the viability of a future definitive trial will be informed by all available data (including process data), as outlined in section 9.7.

Table 5.Progression criteria

|  | **GREEN** | **AMBER** | **RED** |
| --- | --- | --- | --- |
| **Eligibility** | ≥ 70% of people living with MLTCs and frailty are eligible | 69-51% of people living with MLTCs and frailty are eligible | ≤ 50% of people living with MLTCs and frailty are eligible |
| **Recruitment** | ≥ 50% of people living with MLTCs and frailty who were eligible consented to take part in the trial | 49-29% of people living with MLTCs and frailty who were eligible consented to take part in the trial | ≤ 30% of people living with MLTCs and frailty who were eligible consented to take part in the trial |
|  | ≥ 50% of people living with MLTCs and frailty identify a carer who is subsequently recruited into the trial | 49-19% of people living with MLTCs and frailty identify a carer who is subsequently recruited into the trial | ≤ 20% of people living with MLTCs and frailty identify a carer who is subsequently recruited into the trial |
|  | ≥ 20% of participants are from a minority ethnic background | 19-6% of participants are from a minority ethnic background | ≤ 5% of participants are from a minority ethnic background |
|  | ≥ 30% of participants are from socioeconomically deprived backgrounds.  These rates reflect the general population ^128^, ^129^. | 29-8% of participants are from socioeconomically deprived backgrounds. | ≤ 7% of participants are from socioeconomically deprived backgrounds. |
| **Retention** | ≥ 70% of participants retained at 24 weeks | 69-51% of participants retained at 24 weeks | ≤ 50% of participants retained at 24 weeks |
| **Intervention implementation** | ≥ 70% of face-to-face intervention reviews were complete without additional correspondence from the intervention providers | 69-51% of face-to-face intervention reviews were complete without additional correspondence from the intervention providers | ≤ 50% of face-to-face intervention reviews were complete without additional correspondence from intervention providers |
| **Intervention engagement** | Enacts the agreed treatment plan 3 times a week or more on average across the intervention period | Enacts the agreed treatment plan twice weekly on average across the intervention period | Enacts the agreed treatment plan once a week on average across the intervention period |
| **Outcome measure completion** | ≥ 80% of outcome measures completed at 12 and 24 weeks | 79-59% of outcome measures are completed at 12 and 24 weeks | ≤ 60% of outcome measures completed at 12 and 24 weeks |

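### Three rows of the progression table (consent, carer recruitment, outcome completion) have amber and red bands that overlap by one percentage point

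*Protocol*

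**What the plan says.** Section 9.4 of the protocol sets progression criteria in advance. It defines a stop threshold (problems that cannot be resolved) and a go threshold (nothing that would impede a trial). A result between the two calls for change, meaning problems that may be remedied. Table 5 turns this into red, green and amber.

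Three rows matter here:

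- **Consent among eligible people.** Amber: "49-29% of people living with MLTCs and frailty who were eligible consented to take part in the trial". Red: "≤ 30% of people living with MLTCs and frailty who were eligible consented to take part in the trial".
- **Carer recruitment.** Amber: "49-19% of people living with MLTCs and frailty identify a carer who is subsequently recruited into the trial". Red: "≤ 20% of people living with MLTCs and frailty identify a carer who is subsequently recruited into the trial".
- **Outcome completion.** Amber: "79-59% of outcome measures are completed at 12 and 24 weeks". Red: "≤ 60% of outcome measures completed at 12 and 24 weeks".

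The remaining percentage rows are built differently. Eligibility, for example, has amber "69-51% of people living with MLTCs and frailty are eligible" against red at 50% or below, and the ethnicity row has amber "19-6% of participants are from a minority ethnic background" against red at 5% or below.

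Section 9.4 adds that missing the criteria does not by itself rule out a full-scale trial, and that the overall decision draws on all the data. Section 9.7 describes how: quantitative and qualitative results are integrated, compared with the criteria, and taken through the ADePT process.

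**The concern.** In a traffic-light scheme each result should have one colour. In these three rows the lower end of amber lies one point below the top of red, so a narrow range of results carries two labels with different meanings: a problem that can be remedied and one that cannot.

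The rows are not peripheral. Recruitment rate and outcome completion rate are primary outcome measures (section 2.3.1). Carer recruitment also informs whether the definitive trial could have a co-primary outcome for carers (section 7.1.1). If a result fell in an overlap, the table alone would not say which colour to report.

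**Working it through.** No sample size or power figure is involved. The check compares band limits and then asks whether the overlap can be reached.

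**Step 1. Compare the limits.** Amber and red overlap when the amber lower limit is at or below the red cut-off. All limits are from Table 5.

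| Row | Green | Amber | Red | Amber lower limit minus red cut-off | Whole percentages in both |
| --- | --- | --- | --- | --- | --- |
| Eligibility | ≥70 | 51-69 | ≤50 | 51 − 50 = +1 | none |
| Consent | ≥50 | 29-49 | ≤30 | 29 − 30 = −1 | 29, 30 |
| Carer recruitment | ≥50 | 19-49 | ≤20 | 19 − 20 = −1 | 19, 20 |
| Minority ethnic | ≥20 | 6-19 | ≤5 | 6 − 5 = +1 | none |
| Deprivation | ≥30 | 8-29 | ≤7 | 8 − 7 = +1 | none |
| Retention | ≥70 | 51-69 | ≤50 | 51 − 50 = +1 | none |
| Implementation | ≥70 | 51-69 | ≤50 | 51 − 50 = +1 | none |
| Outcome completion | ≥80 | 59-79 | ≤60 | 59 − 60 = −1 | 59, 60 |

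Intervention engagement is stated in times per week, so the check does not apply to it. Five rows start amber one point above red and three start it one point below. That pattern looks like an off-by-one slip.

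**Step 2. Can the overlap be reached?**

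- *Carer row*, with the planned 50 people with MLTCs and frailty (section 9.1): 10/50 = 20.0%, both amber and red. It is the only such count, since 9/50 = 18% is red only and 11/50 = 22% is amber only. For a true rate p, P(X = 10) = C(50,10) p^10 (1 − p)^40. This gives 0.14 at p = 0.20, 0.099 at 0.25, 0.039 at 0.30, 0.001 at 0.40 and 0.015 at 0.10.
- *Consent row*, assuming 50 people consent: the rate is 50/N for N eligible people. It lies between 29% and 30% when N is between 50/0.30 = 166.7 and 50/0.29 = 172.4, so for N = 167 to 172 (29.9% down to 29.1%).
- *Completion row*, assuming a single measure counted over 50 participants: 30/50 = 60%, both amber and red.

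**Step 3. Does the choice of repair matter?** In whole percentages, keeping the red cut-offs gives amber bands of 31-49%, 21-49% and 61-79%. Keeping the amber limits instead gives red at ≤28%, ≤18% and ≤58%. Under the first repair 10/50 carers is red; under the second it is amber. The intended limit therefore has to be confirmed.

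**Step 4. Rounding.** Read literally, whole-number bands leave slivers with no colour, such as 50-51% and 69-70% in the eligibility row; for illustration, 100/198 = 50.5%. The three overlapping rows have the same slivers below green (49-50% and 79-80%). Reporting whole percentages closes them, but does not remove the overlaps in Step 1.

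**The case against.** The strongest reply is that the text of section 9.4 already settles the matter. It sets two thresholds and makes amber whatever lies between them. A result at or below the stop threshold is not between them, so it is red. This stands in good part: it favours red for 10/50 carers. A reader might infer from the table that the colour would have to be chosen after the data are seen. The protocol does not support that, because its prose offers a reading in advance. Even so, the printed amber limits contradict that reading, and the protocol does not say which governs.

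The second reply is that little depends on it. Section 9.4 says that missing a criterion need not rule out a full trial, and section 9.7 bases the decision on integrated evidence. The overlap is one point wide in three of nine rows. The 0.14 for the carer row is near its worst case and falls quickly as the true rate moves away from 20%. The exact 95% interval for 10/50, about 10% to 34%, is far wider than the overlap. All of this stands and keeps the point minor. It softens what a colour leads to, but does not say which colour applies.

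The uncoloured slivers might also be read as a second defect. Every limit in the table is a whole percentage, so they are only a rounding matter, and with a denominator of 50 the percentages move in steps of 2, so no count falls inside one.

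**Conclusion.** The point holds as a minor internal inconsistency. Consent of 29-30%, carer recruitment of 19-20% and outcome completion of 59-60% are each both amber and red in Table 5, contrary to the protocol's own definition of change and to the form of the other five percentage rows. The finding itself rests only on the printed limits. The illustrations assume 50 people enrolled (carer row), 50 consenting (consent row) and a denominator of 50 for one measure (completion row).

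It would be too strong to say that the decision on a definitive trial is left open or could turn on this overlap alone. No analysis or estimate is affected, and the final decision rests on all available data.

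**What to change.** Before results are seen, correct Table 5 so that amber starts above the stated red cut-off, as in the other rows and in line with the text of section 9.4:

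- Consent: green ≥50%, amber >30% to <50%, red ≤30%.
- Carer recruitment: green ≥50%, amber >20% to <50%, red ≤20%.
- Outcome completion: green ≥80%, amber >60% to <80%, red ≤60%.

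The trial team should confirm that the red cut-offs, rather than the amber lower limits, are the intended ones. Writing every percentage row in the same form (green ≥X, amber >Y to <X, red ≤Y) would also remove any dependence on rounding.

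The cost is a wording change to one table, with no effect on participants, data collection or sample size.
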